**LIST OF ABBREVIATIONS AND RELEVANT DEFINITIONS**

|                           |                                                                                                                                                                                                                                                                                                                                                  |
|---------------------------|--------------------------------------------------------------------------------------------------------------------------------------------------------------------------------------------------------------------------------------------------------------------------------------------------------------------------------------------------|
| ABR                | ABR form, General Assessment and Registration form, is the application form that is required for submission to the accredited Ethics Committee (In Dutch, ABR = Algemene Beoordeling en Registratie)                                                                                                                                      |
| AE                 | Adverse Event                                                                                                                                                                                                                                                                                                                             |
| AR                 | Adverse Reaction                                                                                                                                                                                                                                                                                                                          |
| CA                 | Competent Authority                                                                                                                                                                                                                                                                                                                       |
| CCMO               | Central Committee on Research Involving Human Subjects; in Dutch: Centrale Commissie Mensgebonden Onderzoek                                                                                                                                                                                                                               |
| CV                 | Curriculum Vitae                                                                                                                                                                                                                                                                                                                          |
| DM2                | diabetes mellitus type 2                                                                                                                                                                                                                                                                                                                  |
| EE                 | energy expenditure                                                                                                                                                                                                                                                                                                                        |
| F-FDG | F-fluorodeoxy-d-glucose                                                                                                                                                                                                                                                                                                      |
| GCP                | Good Clinical Practice                                                                                                                                                                                                                                                                                                                    |
| IB                 | Investigator's Brochure                                                                                                                                                                                                                                                                                                                   |
| IC                 | Informed Consent                                                                                                                                                                                                                                                                                                                          |
| IMP                | Investigational Medicinal Product                                                                                                                                                                                                                                                                                                         |
| IMPD               | Investigational Medicinal Product Dossier                                                                                                                                                                                                                                                                                                 |
| METC               | Medical research ethics committee (MREC); in Dutch: medisch ethische toetsing commissie (METC)                                                                                                                                                                                                                                            |
| PET CT             | positron emission tomography computed tomography                                                                                                                                                                                                                                                                                          |
| (S)AE              | (Serious) Adverse Event                                                                                                                                                                                                                                                                                                                   |
| SPC                | Summary of Product Characteristics (in Dutch: officiële productinformatie IB1-tekst)                                                                                                                                                                                                                                                      |
| Sponsor            | The sponsor is the party that commissions the organisation or performance of the research, for example a pharmaceutical company, academic hospital, scientific organisation or investigator. A party that provides funding for a study but does not commission it is not regarded as the sponsor, but referred to as a subsidising party. |
| SUSAR              | Suspected Unexpected Serious Adverse Reaction                                                                                                                                                                                                                                                                                             |
| Wbp                | Personal Data Protection Act (in Dutch: Wet Bescherming Persoonsgegevens)                                                                                                                                                                                                                                                                 |
| WMO                | Medical Research Involving Human Subjects Act (in Dutch: Wet Medisch-wetenschappelijk Onderzoek met Mensen)                                                                                                                                                                                                                               |

## SUMMARY

**Rationale:** Obesity and diabetes mellitus type 2 (DM2) are health problems with a tremendous impact. Many attempts have been made to combat obesity and DM2, however, a breakthrough therapy is still lacking.

Obesity is the result of an imbalance between energy intake and energy expenditure.  $^{18}\text{F}$ -fluorodeoxy-d-glucose ( $^{18}\text{F}$ -FDG) positron emission tomography computed tomography (PET-CT) pinpoint areas with high glucose turnover. Physiological  $^{18}\text{F}$ -FDG accumulation is frequently observed in the colon. Therefore, the colon might play an important role in increasing energy expenditure by consuming calories. However, the possibility of the colon as an energy dissipating tissue has not yet been explored. The colon could become an interesting new target of research to find a method to combat obesity.

Metformin is one of the few drugs in the treatment of DM2 that is associated with moderate weight loss. Interestingly, patients using metformin show an increased  $^{18}\text{F}$ -FDG-uptake in the colon. Whether this higher uptake of glucose also cause an increase in core temperature and/or an increase in energy expenditure is not known. The cause for this increase in glucose uptake in the colon by metformin use is unknown. Also, it is unknown whether this increase in glucose uptake results in an increased energy expenditure and/or an increase in core body temperature.

**Objective:** In this study we aim to investigate the influence of metformin (500 mg 1/day) on temperature in the colon, glucose uptake in the colon and energy expenditure in healthy lean ( $\text{BMI} < 24\text{kg/m}^2$ ) or obese subjects ( $\text{BMI} > 28\text{kg/m}^2$ ). We will measure  $^{18}\text{F}$ -FDG uptake in the colon, temperature in the colon, insulin sensitivity and energy expenditure before after using metformin.

**Primary objective:** To investigate whether metformin increases  $^{18}\text{F}$ -FDG uptake in healthy, lean and obese males.

**Secondary Objectives:**

- 1) To investigate whether metformin increases core body temperature in healthy, lean and obese males and whether this correlates with respectively  $^{18}\text{F}$ -FDG uptake.
- 2) To investigate whether metformin increases energy expenditure in healthy, obese males and whether this correlates with respectively  $^{18}\text{F}$ -FDG uptake.
- 3) To investigate whether metformin increases core temperature in healthy, obese males and whether this correlates with respectively  $^{18}\text{F}$ -FDG uptake and energy expenditure.
- 4) To investigate whether metformin increases lactate in healthy obese males and whether there is a correlation between lactate and respectively  $^{18}\text{F}$ -FDG uptake, core body temperature and energy expenditure.

**Study design:** Non-randomized interventional study

**Study population:** 16 healthy male volunteers (aged > 50 years, 8 obese BMI > 28 kg/m^2 and 8 lean BMI < 24 kg/m^2) will be recruited. The volunteers will be recruited by advertisement in local paper and internet (via social media), covering the direct surroundings of our clinic (Amsterdam) and by advertisement at the medical faculty of the AMC.

**Intervention (if applicable):** Participants will use metformin during 7 days

**Main study parameters/endpoints:** Difference in F-FDG uptake in the colon before and after using metformin.

**Nature and extent of the burden and risks associated with participation, benefit and group relatedness:** Included subjects will visit the AMC hospital on 3 occasions.

Visit 1: Informed consent, medical history, vital signs, laboratory measurements.

Total blood drawn: 60 ml. Energy expenditure measurement after 60 minutes rest. Core body temperature measurement (core body pill, tympanic measurement and skin measurement).

F-FDG PET CT. Providing the metformin, start using metformin.

Visit 2 (two weeks after visit 1): Energy expenditure after 60 minutes rest. Core body temperature measurement (core body pill, tympanic measurement and skin measurement).

F-FDG PET CT.

There is no direct benefit for the volunteers. The resulting dose from the radioactive tracers + the scans is 7.8 mSv. The placement of an intravenous canula can be an unpleasant experience and there is a small chance of developing flebitis at the site of the intravenous canula. While using metformin, the subjects can encounter side effects of the metformin. This research will provide insight into the working mechanism of metformin and its potential role in the treatment of obesity.

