## 1. INTRODUCCION and RATIONALE

Obesity and diabetes mellitus type 2 (DM2) are health problems with a tremendous impact. Many attempts have been made to combat obesity and DM2, however, a breakthrough therapy is still lacking.

Obesity is the result of an imbalance between energy intake and energy expenditure. F-fluorodeoxy-d-glucose (F-FDG) positron emission tomography computed tomography (PET-CT) pinpoint areas with high glucose turnover. Physiological F-FDG accumulation is frequently observed in the colon, however, the possibility of the colon as an energy dissipating tissue has not yet been explored. Considering the high uptake of F-FDG in the colon, the colon could have a positive effect on energy balance. Therefore, the colon could become an interesting new target of research to find a method to combat obesity.

Metformin is one of the few drugs in the treatment of DM 2 that is associated with moderate weight loss.

Interestingly, patients using metformin are known to have increased F-FDG-uptake in the colon. A substantial number of subjects (e.g 42%) show an increased F-FDG uptake without the use of metformin. Nonetheless, in a matched case-control analysis, the use of metformin significantly increased physiological accumulation of F-FDG in the colon. Also, discontinuation of metformin in the 2 days before the F-FDG PET-CT, significantly diminished the high F-FDG uptake in the colon. Indeed, the colon has been shown to be a site of increased glucose utilization during metformin treatment in mice. The cause for this increase in glucose uptake in the colon by metformin use is unknown. A possible explanation for increased glucose uptake might be the shift from aerobic to anaerobic glucose metabolism due to the inhibition of the mitochondrial respiratory complex I during metformin use. This mechanism has been proposed as a possible cause of changed intestinal glucose handling and increased production of lactate. This less efficient metabolism might in turn lead to increased heat dissipation. It is unknown whether this increase in glucose uptake in the colon results in an increased energy expenditure and/or an increase in core body temperature.

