### 3. STUDY DESIGN

In this non-randomised intervention study we will study the influence of metformin (1000 mg/day (500 mg in the morning, 500 mg in the evening) during 1 week) on  $^{18}\text{F}$ -FDG uptake in the colon. The main outcome will be difference in  $^{18}\text{F}$ -FDG uptake. Furthermore, we will measure core body temperature, energy expenditure and HOMA-index. 16 healthy volunteers of Caucasian origin will be included (8 lean, BMI < 24 kg/m^2 and 8 obese BMI > 28 kg/m^2) in this study. Subjects (n=16) will be investigated before and after using metformin (1000 mg/day during 1 week). Included subjects will visit the AMC hospital on three occasions. Below is a description of each visit.

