#### Study visits and procedures

During the **first** study visit, participants will come to the AMC for screening to determine eligibility for the study. During this visit, informed consent will be obtained after oral and written explanation of the study. Subsequently, length, weight, waist circumference and medical history will be acquired. In total, a maximum of 20 ml of blood will be drawn to perform laboratory measurements needed to determine eligibility for the study (kidney function and liver function). The chronic use of drugs and/or medication will be asked at the participant. If eligible, the second visit will be scheduled.

The **second and third visit** are similar. Core body temperature will be measured using a body core pill and tympanic temperature will be measured every 15 minutes. Blood will be drawn to measure insulin sensitivity, in total 40 ml of blood will be drawn to be able to perform blood tests and as stored serum. After 60 minutes an energy expenditure (EE) will be performed using indirect calorimetry. Glucose uptake in the colon will be evaluated using  $^{18}\text{F}$ -FDG PET CT.

After the **second** visit, subjects will receive the metformin and information on how to use this.

**Flow chart;** overview of the procedures that subjects will undergo in the course of the study.

[figure not shown]

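### The Summary sets the post-metformin PET two weeks after a visit at which a 7-day course begins: read literally, about a week off drug

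*Protocol*

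**What the plan says.** **Summary.** The intervention line reads "Participants will use metformin during 7 days". The paragraph on burden and risks announces "Included subjects will visit the AMC hospital on 3 occasions" but then describes only two visits. Visit 1 holds consent, medical history, laboratory work, calorimetry, temperature and the baseline PET-CT, and closes with "Providing the metformin, start using metformin". The next entry is "Visit 2 (two weeks after visit 1): Energy expenditure after 60 minutes rest", followed by temperature and the second PET-CT. Visit 1 also carries "Total blood drawn: 60 ml".

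**Section 1.** The rationale cites a study in which "discontinuation of metformin in the 2 days before the" PET-CT significantly lowered the high colonic uptake.

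**Section 3.** There are three visits. At the first, "participants will come to the AMC for screening to determine eligibility for the study". The second and third hold the same measurements, and metformin is handed out after the second. Subjects "will be investigated before and after using metformin (1000 mg/day during 1 week"). The text gives no number of days between the second and third visits; the flow chart is not visible.

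**Sections 5.1 and 7.1.1.** Dosing is 500 mg morning and evening for 7 days. The primary endpoint is the difference in FDG uptake before and after those 7 days of daily use.

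**The concern.** The second PET is the primary measurement, and the effect sought is uptake while metformin is being taken. By the protocol's own rationale, that effect fades soon after the drug is stopped. A visit date that leaves about a week between the last dose and the scan would compare untreated uptake with largely washed-out uptake, which pulls the estimated change towards zero. The calorimetry and temperature readings listed for the same visit would also be taken off drug. No objective in the protocol concerns washout or persistence, so nothing would justify such a gap. A coordinator who books PET slots from the Summary would find only this interval to work from.

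**Working it through.** The point rests on day counting; no sample-size or power figure enters it.

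**Inputs**
- Baseline PET, then start of metformin: Visit 1, day 0 (Summary).
- Course: 7 days, two doses a day, so 7 × 2 = 14 doses (Section 5.1).
- Second PET: day 14 (Summary, two weeks after Visit 1).
- Stop known to lower uptake: 2 days (Section 1).
- Assumed clock times, not in the protocol: doses at 08:00 and 20:00, scans between 08:00 and 16:00.

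**Time of last dose.** Fourteen doses 12 hours apart span 13 × 12 = 156 h. Hours are counted from midnight at the start of day 0. Because the baseline PET comes before the first dose, the earliest start is taken as that evening.
- First dose evening of day 0 (20 h): last dose at 20 + 156 = 176 h, the morning of day 7.
- First dose morning of day 1 (32 h): last dose at 32 + 156 = 188 h, the evening of day 7.

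**Time off drug at a day-14 scan.** The scan falls between 14 × 24 + 8 = 344 h and 14 × 24 + 16 = 352 h.

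| First dose | Scan at 08:00 | Scan at 16:00 |
|---|---|---|
| Evening, day 0 | 344 − 176 = 168 h (7.0 days) | 352 − 176 = 176 h (7.3 days) |
| Morning, day 1 | 344 − 188 = 156 h (6.5 days) | 352 − 188 = 164 h (6.8 days) |

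The range is 6.5 to 7.3 days. Against the 2 days in Section 1, 6.5 / 2 = 3.25 and 7.3 / 2 = 3.65, so more than three times in every case.

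The Summary's objective paragraph gives 500 mg once a day, which disagrees with Sections 3, 5.1 and 6.6; the twice-daily regimen is used here. Seven once-daily doses would span 6 × 24 = 144 h, so the course would end 12 h earlier and each gap would grow by half a day, with the same conclusion.

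**Is the Summary list reliable?** Section 3 draws at most 20 ml at screening and 40 ml in total for the later visits: 20 + 40 = 60 ml, which is the whole-study total in Section 7.2. The Summary attaches that 60 ml to Visit 1, where it also places consent and eligibility work beside the baseline PET. Together with three visits announced and two described, this shows that screening and baseline were merged.

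**If two weeks was counted from screening.** The scan would then fall at the end of the course only if baseline came 14 − 7 = 7 days after screening. The readable text does not say this; Section 3 says only that the second visit is scheduled once the subject is found eligible.

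**A scan on day 7.** It falls between 7 × 24 + 8 = 176 h and 7 × 24 + 16 = 184 h. With the first dose on the evening of day 0, that is 0 to 8 h after the fourteenth dose.

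**The case against.** The strongest reply is that this is a synopsis error in a paragraph about burden. The operative sections describe three visits, a 7-day course and an endpoint tied to that course; Section 7.2 sends the reader to the Study Design section for procedures; and none of them sets a washout. The list is visibly wrong about Visit 1, so a literal count from Visit 1 leans on its least reliable part. Screening, a week to baseline, then a week on drug is a natural reading, and the flow chart may show exactly that. Section 1 is background and not a schedule, and the title of the study it cites concerns diabetic patients on metformin, not healthy volunteers.

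Most of this stands, and it settles what kind of problem this is: an inconsistency to be corrected, not a design decision to be contested. It does not remove the problem. The readable body of the protocol gives no other interval, and a correct flow chart would still contradict the Summary.

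Three stronger readings are tempting but not supported:
- **That the trial plans an off-drug scan.** No section says so, and the sense of Sections 3 and 7.1.1 is against it. Nor can it be said that Section 3 leaves the scan day unset, because its flow chart cannot be seen.
- **That the gap reaches 8 days.** Whole calendar days suggest this, but 14 twice-daily doses ending on the evening of day 6 would need a morning dose on day 0, and the Summary starts metformin after the baseline PET.
- **That a loss of SUV or power can be stated.** The protocol does not give the size of the effect of stopping metformin, so any such figure would rest on an assumed retained fraction.

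**Conclusion.** The inconsistency is real and should be corrected. The Summary's timing, taken literally, puts the primary measurement about 6.5 to 7.3 days after the last dose, given twice-daily dosing begun after the baseline PET and ordinary clinic hours. It does not fit the endpoint definition, and it sits badly with the rationale. The most likely cause is a merged visit list, with the two weeks perhaps counted from screening. The bias towards no effect arises only if the Summary is followed, and its size cannot be derived from the document. It is still more than a clerical matter, because the interval decides what the primary endpoint measures. Confidence is moderate, since the flow chart may already give the intended days.

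**What to change.** - Rewrite the Summary's visit list as the three visits of Section 3: screening, baseline, post-metformin.
- Replace the two-week interval with a post-metformin visit on the last day of the 7-day course, about day 7 after baseline and within hours of the last dose. A first dose on the evening of the baseline visit achieves this.
- State the same timing in Sections 3 and 7.1.1, and check that the flow chart agrees.
- Set the start of dosing from the booked scan date. If a slot moves before dosing begins, move the start with it. Open-ended extra dosing would alter the 7-day exposure fixed in Sections 5.1 and 7.1.1.
- Record the time since last dose at the second PET for every subject, so that departures can be seen.

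The cost is protocol wording and visit booking, with no extra visit, scan or radiation.
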